**The following information should be provided to accurately and completely record the event:**

- 1) Investigator name
- 2) Patient number
- 3) Patient initials
- 4) Patient demographics
- 5) Clinical event
  - Description of the event
  - Date of onset
  - Severity of the event
  - Treatment
  - Relationship to study catheter (causality)
  - Actions taken regarding study catheter
- 6) If the AE results in Death
  - Cause of death (whether or not the death is related to study catheter)
  - Autopsy findings (if available)
- 7) Medical history CRF (copy)
- 8) Concomitant medication case report (copy of relevant CRF page )
- 9) Any relevant reports (laboratory, discharge, x-Ray, etc.)

This information should be sent to the sponsor.

The procedures for notification of suspected serious unexpected adverse reactions (SUSARs) shall be carried out in accordance with the Israeli MOH. SAEs should be reported by the ENOX BIOPHARMA to EC/IRB according to local requirements.

Patients who have had an SAE during the treatment period must be followed clinically until all parameters (including laboratory) have either returned to normal or have stabilized or are otherwise explained.

Any newly emergent SAEs, after treatment is discontinued or the patient has completed the study and is considered to be related to the investigational medicinal product (IMP) or study participation, should be recorded and reported immediately. The post-study period for the purpose of SAE reporting is routinely up to 30 days following last study visit or until SAE is resolved or stabilized.

### 13. STATISTICAL METHODOLOGY

#### **General:**

All measured variables and derived parameters will be listed individually and, if appropriate, tabulated by descriptive statistics.

For categorical variables summary tables will be provided giving sample size, absolute and relative frequency, and 95% CI for proportions, by study group.

For continuous variables summary tables will be provided giving sample size, arithmetic mean, standard deviation, coefficient of variation (if appropriate), median, minimum and maximum, percentiles, and 95% CI for means of variables, by study group.

#### **Safety and Tolerability:**

The study objective is to demonstrate a safety and tolerability profile.

Adverse events will be coded according to coding dictionaries (MedDRA version 16.1 or higher) and presented in tables by System Organ Class (SOC) and Preferred Term (PT). Additional tables will be generated for adverse events associated with NO-impregnated catheters.

95% CI will be calculated for the proportion of patients who prematurely discontinued the study for any reason and due to any AE or SAE.

Chi-square test or Fisher's Exact test (as is appropriate) will be used for analyzing the difference in proportions between the study groups. Laboratory results will be summarized in appropriate tables by time. Changes from baseline will be calculated and presented as well.

#### **Observational Assessment**

95% CI will be calculated for the proportion of patients with catheter-related urinary tract infections at any time point.

Chi-square test or Fisher's Exact test (as appropriate) will be used for analyzing the difference in the above proportions between the study groups.

The Paired T-test or Signed Rank test for two means (paired observations; as is appropriate) will be applied for testing the statistical significance of the changes from baseline to any post-baseline measurement in biofilm formation on the surface and bacteriuria within study group.

The two-sample T-test or Non-parametric Wilcoxon-Mann-Whitney Rank sum test for independent samples (as appropriate) will be applied for testing the statistical significance of the differences in the above parameters between the study groups.

All tests will be two-tailed, and a *p-value* of 5% or less will be considered statistically significant.

The data will be analyzed using the SAS ® version 9.1 (SAS Institute, Cary North Carolina).

### 13.1 Sample Size Rationale

Total of 12 patients.

The planned sample size of 12 patients for the Phase I trial took under consideration the possibility of a 10% drop, as detailed in section 7.5. The planned sample size considered adequate by the sponsor and investigators for this study. The study is not expected to show statistical significance or statistical power, only demonstrate a safety profile.

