## 6. STUDY DESIGN

### 6.1 Overview and Plan

This is a Prospective, Phase I, Open-label Case Series, Single-Center study.

A total of 12 patients, over the age of 18, undergoing radical prostatectomy will be enrolled. Screening data will be reviewed to determine patients' eligibility and informed consents will be obtained.

Patients who meet all inclusion criteria and none of the exclusion criteria will be enrolled.

6 patients will be allocated to receive NO-impregnated Foley catheters (treatment) followed by 6 patients allocated to receive non-NO-impregnated Foley catheters (control).

A patient will receive catheter up to  $21 \pm 7$  days of study treatment. A patient is considered as completed the study "per protocol", once study treatment was completed: 30-45 days after catheterization.

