### **7.5.4 Replacement of Withdrawn Patients**

Up to 12 patients will be recruited, in order to have a sample size of at least 6 patients catheterized with NO-impregnated catheters and 6 patients catheterized with non-NO-impregnated catheters, who completed the study (see protocol).

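### The 12-patient sample size is said to allow for a 10% drop, but recruitment stops at 12 and 12 completers are required, so the allowance is zero

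*Protocol*

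**What the plan says.** Section 13.1 (Sample Size Rationale) gives 12 as the total and states: "The planned sample size of 12 patients for the Phase I trial took under consideration the possibility of a 10% drop". For the detail it points to section 7.5. It adds that the sponsor and investigators considered the size adequate, and that neither statistical significance nor power is expected.

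Within section 7.5, only 7.5.4 (Replacement of Withdrawn Patients) deals with numbers. It sets a ceiling: "Up to 12 patients will be recruited". The purpose it gives is a minimum of 6 in the nitric oxide group and, as controls, "6 patients catheterized with non-NO-impregnated catheters, who completed the study".

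The total is the same elsewhere. Section 6.1 says "A total of 12 patients, over the age of 18, undergoing radical prostatectomy will be enrolled", split 6 and 6, with the treatment group filled first. The synopsis (Study Design, Number of Patients) and section 7.1 repeat 12 as 6 + 6. No larger recruitment figure appears anywhere.

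**The concern.** A drop-out allowance is the gap between the number recruited and the number who must complete. Section 13.1 says that 12 contains such a gap. Section 7.5.4 sets the ceiling on recruitment and the floor on completers at the same number, which leaves no gap. Both statements cannot be true.

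The cross-reference does not help. Sections 7.5 to 7.5.4 cover discontinuation, withdrawal, study stop and replacement, but none of them mentions 10%, extra patients or how a withdrawn patient would be replaced. Despite its heading, 7.5.4 leaves nobody to replace with. Under a cap of 12, an extra treatment patient could come only at the expense of a control, which moves the shortfall to the other group.

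The protocol therefore states a property that the design lacks. Once one patient withdraws, the site cannot meet 7.5.4 and has no instruction on what to do next.

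**Working it through.** **Inputs**
- Recruitment: at most 12 (7.5.4); 12 enrolled as 6 + 6 (6.1, 7.1, synopsis).
- Required completers: at least 6 + 6 = 12 (7.5.4).
- Drop-out allowance claimed: 10% (13.1).
- Effect size and power: none given, so no power formula applies.

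**Step 1: the allowance actually present.** Recruited minus required = 12 − 12 = 0 patients, or 0%. One withdrawal is 1/12 = 8.3%, less than the 10% said to be covered, and it already makes the target unreachable.

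**Step 2: can 12 be reproduced with a 10% allowance?** The usual inflation is n / (1 − d), rounded up, with d = 0.10.
- Target of 10 completers: 10 / 0.9 = 11.1, so 12. This reproduces the stated total.
- Target of 11 completers: 11 / 0.9 = 12.2, so 13.
- Target of 12 completers: 12 / 0.9 = 13.3, so 14. Per group, 6 / 0.9 = 6.7, so 7.

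Twelve therefore contains a 10% allowance only for a target of 10 completers, and 7.5.4 asks for 12.

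**Step 3: what 12 recruited would deliver.** Expected completers at 10% are 12 × 0.9 = 10.8 in total, or 6 × 0.9 = 5.4 per group.

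The probability that all 12 complete, assuming independent withdrawals with the same probability for every patient, is (1 − d)^12:

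| Drop-out | Calculation | P(all 12 complete) |
|---|---|---|
| 5% | 0.95^12 | 54% |
| 10% | 0.90^12 | 28% |
| 20% | 0.80^12 | 7% |

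The protocol gives only the 10%; the 5% and 20% rows are assumed, to show the range. For one group at 10%, 0.9^6 = 53%.

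**Step 4: what a higher cap would buy.** On the same assumptions at 10%, with 7 per group the chance of at least 6 completers in one group is 0.9^7 + 7 × 0.9^6 × 0.1 = 0.850, and in both groups 0.850² = 72%. With 8 per group the figures are 0.962 and 93%. Inflating to 14 makes 12 completers the expected order of magnitude; it does not guarantee them.

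**The case against.** The best defence is that little depends on this. Section 13.1 does not derive 12 from power or precision, the aim is a descriptive safety profile, and no analysis or decision rule requires 6 + 6 completers. Ending with 10 or 11 invalidates nothing planned. That stands, and it limits the severity.

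It can also be said that the 10% is only a possibility considered in planning, not a predicted rate, and that independence is an assumption. That stands too. The probabilities in the working are illustrations, and at 5% the full target is met slightly more often than not. The contradiction itself uses no probability.

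A milder reading is that 12 are enrolled and 10 or 11 completers are acceptable. This may be what was meant, but the completer requirement in 7.5.4 says otherwise.

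A reader might infer something stronger: that the site will quietly replace men withdrawn for adverse events, leaving a set of completers selected for good tolerance. The protocol does not support this. Nothing in it says that such substitution will occur, and withdrawal is itself an outcome. Discontinuation due to adverse events is a primary endpoint (5.1), section 13 gives it a confidence interval, and 13.4 tabulates non-completion with Kaplan-Meier curves for time to withdrawal. The intent-to-treat cohort in 13.3 keeps everyone with at least one day of catheter treatment, whether or not he completes. A man withdrawn for insertion difficulty before that first day could fall outside the cohort, but this follows from the cohort definition and is a separate matter from the sample-size statement.

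**Conclusion.** The point holds as an internal contradiction. Section 13.1 claims a 10% drop-out allowance; taken with 7.5.4 the allowance is zero, and the section cited for the detail does not supply it. This rests on the protocol's own counts alone. The size of the shortfall (10.8 completers expected, and a 28% chance of all 12 at 10%) rests in addition on independent withdrawals at a common rate.

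Severity is minor to moderate. It would be wrong to infer that the trial is underpowered, since no power is claimed, or that it must recruit 14, since dropping the completer requirement resolves the conflict equally well. What needs correcting is a stated property of the sample size that the design does not have.

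**What to change.** Reconcile 13.1 and 7.5.4. The simplest route adds no patients:

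- In 13.1, delete the claim that 12 includes a drop-out allowance, together with the reference to 7.5.
- In 7.5.4, replace the requirement for 6 + 6 completers with: *Twelve patients are enrolled (6 per group). At 10% drop-out about 10 to 11 completers are expected; 6 completers per group is not guaranteed.*

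This costs two sentences and a slightly less favourable completer figure.

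If the sponsor did intend replacement, 7.5.4 must state a recruitment cap above 12 and say that replaced patients remain in the intent-to-treat and safety analyses. The totals in the synopsis, 6.1, 7.1 and 13.1 would have to follow. A cap of 14 would cost up to two more patients and, as shown in the working, would still leave the target uncertain. The choice is the sponsor's; either route removes the contradiction.

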| 
Statistical Considerations:
 | 
All measured variables and derived parameters will be listed individually and, if appropriate, tabulated by descriptive statistics. For categorical variables summary tables will be provided giving sample size, absolute and relative frequency and 95% Confidence Interval (CI) for proportions by study group.
 
For continuous variables summary tables will be provided giving sample size, arithmetic mean, standard deviation, coefficient of variation (if appropriate), median, minimum and maximum, percentiles and 95% CI for means of variables by study group.
 
Statistical Methods:
 
The study objective is to demonstrate a safety profile and tolerability. All adverse events will be coded according to coding dictionaries (MedDRA version 16.1 or higher) and presented in tables by System Organ Class (SOC) and Preferred Term (PT). Drug-related adverse events will be presented as well.
 
95% CI will be calculated for the proportion of patients who prematurely discontinued the study for any reason and due to any AE or SAE.
 
Chi-square test or Fisher's Exact test (as is appropriate) will be used for analyzing the difference in proportions between the study groups. The Paired T-test or Signed rank test for two means (as is appropriate) will be applied for analyzing changes in continuous parameters within study group.
 
The two-sample T-test or Non-parametric Wilcoxon-Mann-Whitney Rank sum test for independent samples (as is appropriate) will be applied for analyzing differences in continuous parameters between the study groups.
 
All tests will be two-tailed, and a p-value of 5% or less will be considered statistically significant.
 
The data will be analyzed using the SAS ® version 9.1 (SAS Institute, Cary North Carolina).
 |

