**3.2 Study Hypothesis**

NO-impregnated Foley catheters indwelled for  $7-21 \pm 7$  days are safe and tolerable.

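### Six NO-catheter patients cannot support a claim of safety and tolerability: the planned 95% intervals have no criterion, and 5% between-group tests stay in after significance is disclaimed

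*Protocol*

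**What the plan says.** - **Hypothesis.** Protocol Section 3.2 states that NO-impregnated catheters, left in for the planned period, "are safe and tolerable". No acceptable rate, margin or limit is attached there or elsewhere.
- **Aim and disclaimer.** Section 13.1: "The study is not expected to show statistical significance or statistical power, only demonstrate a safety profile". Section 7.1 and the Synopsis (Number of Patients) say much the same. Section 13 (Safety and Tolerability) again gives demonstrating such a profile as the objective.
- **Design.** Section 6.1 assigns six patients to the NO catheter and then six to control, without randomisation (Sections 8.2 and 13.2).
- **Intervals.** Section 13 plans 95% confidence intervals for proportions by study group, and adds: "95% CI will be calculated for the proportion of patients who prematurely discontinued the study for any reason and due to any AE or SAE".
- **Tests.** The same part of Section 13 says: "Chi-square test or Fisher's Exact test (as is appropriate) will be used for analyzing the difference in proportions between the study groups". Section 13.4 (Tolerability Assessments) adds significance testing of time to withdrawal with a Cox model.
- **Threshold.** The Synopsis says: "All tests will be two-tailed, and a p-value of 5% or less will be considered statistically significant". Section 13 repeats this at the end of Observational Assessment, again for all tests.
- **Primary endpoints.** Section 5.1 lists AEs and SAEs associated with the NO catheter, discontinuation because of AEs or SAEs, and discontinuation because of AEs or SAEs associated with the NO catheter.

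**The concern.** The protocol sets three things side by side that do not fit together:

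1. A hypothesis worded as a conclusion about the device.
2. A statement that significance is not expected.
3. Significance tests on safety and tolerability with a 5% threshold.

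The intervals could carry the safety conclusion, but nothing says what upper limit would be acceptable. That leaves the p-value as the only numerical threshold for inference in the document. Section 13 and Section 3.2 fix these elements in the protocol itself, so a separate analysis plan would inherit the conflict.

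At stake is what may be concluded from a first use in humans (Appendix 5). A report that finds no significant difference, set beside an aim of demonstrating safety, would sound far more reassuring than six exposed patients can justify.

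**Working it through.** **The plan's own figure.** The total of 12 rests on the judgement of the sponsor and investigators (Section 13.1). No effect size, event rate, margin or power is given, so there is no calculation to reproduce.

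**Inputs.** From the protocol: 6 patients per arm (Section 6.1), two-sided 5% (Synopsis, Section 13), chi-square or Fisher as appropriate (Section 13). Assumed here because the protocol gives none: the true event risks used in step 4.

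**Step 1: what the best possible result excludes.** The exact (Clopper-Pearson) two-sided 95% upper limit for 0 events in n is 1 − 0.025^(1/n).

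- 0/6: 1 − 0.025^(1/6) = 45.9%. The one-sided 95% limit is 1 − 0.05^(1/6) = 39.3%.
- 1/6: the upper limit solves (1 − p)^6 + 6p(1 − p)^5 = 0.025, giving 64.1%.
- If only five NO patients were evaluable, 0/5 gives 1 − 0.025^(1/5) = 52.2%.

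Conversely, with a true risk of 20%, a clean 0/6 occurs with probability 0.8^6 = 26%. None of these limits depends on an assumed control rate.

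**Step 2: which test applies.** Within an arm of 6, the expected counts with and without the event sum to 6. At least one is therefore always below 5, and Fisher's test is the appropriate choice under Section 13.

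**Step 3: what Fisher's test needs.** Two-sided p-values at 6 versus 6:

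| NO arm | Control | p |
|---|---|---|
| 4/6 | 0/6 | 2 × 15/495 = 0.061 |
| 5/6 | 0/6 | 2 × 6/792 = 0.015 |
| 6/6 | 0/6 | 2 × 1/924 = 0.002 |
| 5/6 | 1/6 | 0.080 |
| 6/6 | 1/6 | 2 × 6/792 = 0.015 |

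In the direction of harm, only 5/6 v 0/6, 6/6 v 0/6 and 6/6 v 1/6 reach 5%.

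**Step 4: how often that happens.** Assume a risk of 10% in control and 50% in the NO arm.

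- Control: P(0) = 0.9^6 = 0.531; P(1) = 6 × 0.1 × 0.9^5 = 0.354.
- NO arm: P(5) = 6 × 0.5^6 = 0.0938; P(6) = 0.5^6 = 0.0156.
- Power = 0.531 × (0.0938 + 0.0156) + 0.354 × 0.0156 = 0.0581 + 0.0055 = 6.4%. The opposite tail adds a negligible amount.

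The test therefore misses this difference 93.6% of the time. Other assumed pairs:

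| Control v NO risk | Power | Miss |
|---|---|---|
| 10% v 30% | 0.6% | 99% |
| 20% v 50% | 3.5% | 97% |
| 10% v 50% | 6.4% | 94% |
| 10% v 70% | 26.5% | 74% |

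**Step 5: dependence on the test.** At 10% v 50% the continuity-corrected chi-square gives the same 6.4%. The uncorrected chi-square gives 39.0% (a 61% miss), but it is not appropriate at these counts. No power figure was computed for the Cox test.

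**Step 6: dependence on the interval method.** At 0/6 the upper limit is 45.9% exact, 44.3% Agresti-Coull and 39.0% Wilson. The simple normal interval collapses to 0% to 0%. Section 13 names no method. That may belong in the analysis plan, but the choice matters here.

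**The case against.** The strongest defence is that this is an openly unpowered Phase I case series. Section 13.1 admits as much, and showing that 6 versus 6 has little power only restates the admission. That stands: low power is not the fault here, and nothing below asks for more patients.

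A reader might go further and infer that the protocol treats a non-significant test as its rule for declaring the catheter safe. The documents do not support that. Section 13 applies the test to the difference in proportions and defines when a result is called significant; it never says what follows from non-significance.

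Nor is it right that no upper bound is planned. The intervals by group supply one; what is missing is a criterion for reading it.

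Several primary endpoints concern only the NO arm and have no control counterpart. The protocol also plans causality grading, tables of catheter-associated events and case-by-case discussion of SAEs (Sections 12, 13 and 13.4). Safety judgement therefore does not rest on a two-group test alone. Moreover, most of the aim statements speak of a profile, which can be read as description.

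What this defence leaves unanswered is Section 3.2, which goes beyond description, and the tests kept in Sections 13 and 13.4 after significance has been disclaimed.

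**Conclusion.** The point holds as a mismatch between claim and design. Six NO patients cannot establish that the device is safe and tolerable: a result with no events still leaves rates up to about 46% inside the two-sided 95% interval, and one event leaves rates up to about 64%. Those limits rest only on six evaluable patients and the exact method.

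The between-group tests do not fill the gap. A non-significant Fisher result carries almost no information at this size, missing about 94% at 10% v 50% and between 74% and 99% across the pairs examined. Those miss rates rest on assumed risks that the protocol does not give, and on Fisher's test being the one used.

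The planned descriptive safety analyses are sound in kind. The fault lies in the wording of the hypothesis and aim, the retained significance tests, and the absence of any criterion for the intervals. It is worth correcting because it governs what the trial may conclude.

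**What to change.** 1. In Sections 3.2, 7.1, 13 and 13.1, and the matching Synopsis text, restate the aim as describing safety and tolerability and estimating event rates.
2. In Section 13, remove the chi-square/Fisher significance test for safety and tolerability proportions, and in Section 13.4 the Cox significance test. Alternatively, label both as descriptive only.
3. Make the exact (Clopper-Pearson) 95% interval in the NO arm the basis of the safety statement.
4. Add to Section 13.1: *With 0 of 6 events, only rates above about 46% are excluded (two-sided 95% limit); absence of a significant difference will not be taken as evidence of safety.*

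This is a change of wording and of analysis labels. It needs no new patients, data or procedures. The downside is that the claim the sponsor may make becomes less favourable.

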### 13.2 Randomization

N/A

### 13.3 Patient Cohorts

#### **Intent-to-Treat Cohort (ITT):**

The ITT cohort includes all patients who receive at least one day of catheter treatment.

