### 3.3 Summary

This study proposes to use NO-impregnated catheters takes into consideration previous knowledge of:

- (a) The known infection prevention properties of NO-impregnated catheters (ENOX innovation method).
- (b) Nitric oxide activity as vasodilator.
- (c) NO's very short half-life within the blood system, which minimize the time of active NO presence in the blood and its potential hazard to distal organs.
- (d) NO-impregnated catheters have a safe profile in a rabbit model.
- (e) Long term use of NO in a gas formation which has been approved by FDA to treat premature infants through mechanical respiratory rout.

NO-impregnated catheter method was developed by ENOX to prevent nosocomial infection. Bacterial colonization rates in catheterized patients are high. Moreover, bacterial density and biofilm formation in the catheter is high and consistent for days/weeks (but tend to increase over time). NO-impregnated catheters reduces bacterial density and can prevent biofilm formation [16], and were found to be safe in animal trials.

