### **7.5.2 Criteria for Early Study Withdrawal**

A patient may withdraw or be withdrawn from the study for the following reasons:

- 1) Patient withdrew consent.
- 2) Protocol violation/ non-compliance.
- 3) Loss to follow-up/failure to return.
- 4) Patient with difficulty in insertion of catheter during surgery.
- 5) In cases which require catheter replacement.
- 6) Serious adverse event

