## **11.4 Safety Parameters**

### **11.4.1 Adverse Events**

Adverse events will be recorded from the date of patients signed informed consent form and throughout the study, including the follow-up period. They should be reviewed and updated at each subsequent visit and during any phone contact with the patient.

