#### **Completer Cohort:**

The Completer cohort includes all patients in the ITT cohort who complete the study.

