#### **Per Protocol Cohort:**

The Per-Protocol cohort includes all patients in the ITT cohort who complete the study (completed study treatment) in compliance with the protocol and have no major protocol violations.

For the ITT cohort, the Last Observation Carried Forward (LOCF) approach will be applied, when deemed appropriate, to account for missing data at or prior to study termination.

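### Every cohort named in section 13.3 requires at least one day of catheterisation, so an early device failure can drop out of the tabulated primary safety and tolerability proportions

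*Protocol*

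**What the plan says.** Protocol section 13.3 names three cohorts:

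- Intent-to-treat: "The ITT cohort includes all patients who receive at least one day of catheter treatment".
- Completer: "The Completer cohort includes all patients in the ITT cohort who complete the study".
- Per-protocol: "The Per-Protocol cohort includes all patients in the ITT cohort who complete the study", with the further conditions of compliance and no major violations.

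On missing data it adds: "For the ITT cohort, the Last Observation Carried Forward (LOCF) approach will be applied, when deemed appropriate, to account for missing data".

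Section 7.5.2 lists among its reasons for withdrawal "Patient with difficulty in insertion of catheter during surgery" and "In cases which require catheter replacement".

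Section 11.4.1 sets the collection window: "Adverse events will be recorded from the date of patients signed informed consent form and throughout the study, including the follow-up period".

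The primary endpoints in section 5.1 are adverse events associated with the NO catheter, the proportion discontinuing because of any adverse event, and, for tolerability, the proportion discontinuing because of an adverse event associated with that catheter. Section 13 promises 95% confidence intervals for discontinuation overall and for adverse events. Section 13.4 bases tolerability on the number and percentage who do not complete. None of these passages names the cohort that supplies the denominator.

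**The concern.** Receiving at least one day of catheter treatment is known only after insertion, and it depends on how the device performs. A safety denominator built on it is conditioned on something close to the outcome. The patients most likely to fall short are those with a failed or traumatic insertion, or with removal in the first hours. These are among the cases that a first study in humans of a new device exists to find.

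The rule is written into the protocol, and section 20.2 commits the statisticians to the analysis that the protocol defines. It also sits badly with the data collection, which starts at consent and covers patients whom none of the three cohorts admits. If one of these cohorts becomes the denominator by default, a single early failure in a group of 6 can turn a non-zero primary proportion into zero.

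The secondary concern is LOCF. Section 3.3 says of catheterised patients that "bacterial density and biofilm formation in the catheter is high and consistent for days/weeks (but tend to increase over time". An early culture carried to the removal visit would then tend to understate bacteriuria there. The choice of when to apply it is left open in an open-label study.

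**Working it through.** **What there is to reproduce.** The sample size of 12 is a judgement (section 13.1). No event rate, effect or power is given, so there is no design calculation to repeat. The check concerns cohort membership and what one exclusion does to a proportion.

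**Step 1: cohort membership.** Take three hypothetical patients against section 13.3.

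| Patient | ITT | Completer | Per-protocol |
|---|---|---|---|
| Insertion attempted and failed, withdrawn under 7.5.2 | No | No (subset of ITT) | No (subset of ITT) |
| Inserted, removed within hours | No, if one day means 24 hours; arguable if any catheterisation on day 1 counts | No, if not in ITT | No, if not in ITT |
| Removed on day 3 | Yes | Only if he completes the study | Only if he completes treatment and study without major violation |

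The first patient is outside all three under any reading. The second depends on a definition of one day that the protocol does not give.

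**Step 2: effect on the proportion.** Inputs: 6 patients per group (section 7.1), and no replacement of the excluded patient (section 7.5.4 caps recruitment at 12). The protocol does not name an interval method, so the exact Clopper-Pearson interval is my choice: lower limit = 2.5% quantile of Beta(x, n−x+1), upper limit = 97.5% quantile of Beta(x+1, n−x). For x = 0 the lower limit is 0 and the upper limit is 1 − 0.025^(1/n). For x = 1 the lower limit is 1 − 0.975^(1/n).

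One NO-arm patient loses the catheter within a day and discontinues for an adverse event; no other patient does:

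- Counted: 1/6 = 16.7%. Lower limit 1 − 0.975^(1/6) = 0.004; upper limit 0.641.
- Excluded: 0/5 = 0%. Upper limit 1 − 0.025^(1/5) = 0.522.

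Two such patients:

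- Counted: 2/6 = 33.3% (4.3 to 77.7%).
- Excluded: 0/4 = 0% (0 to 60.2%).

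**Step 3: how likely at least one such patient is.** The protocol gives no early-failure rate, so this is an assumption shown over a range. With 6 patients and rate p, the probability is 1 − (1 − p)^6:

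- p = 5%: 1 − 0.95^6 = 26%
- p = 10%: 1 − 0.90^6 = 47%
- p = 20%: 1 − 0.80^6 = 74%

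**Step 4: the between-group test.** With no events among 6 controls, Fisher's exact test gives p = 1.0 both for 1/6 against 0/6 and for 0/5 against 0/6. The exclusion changes the reported rate and its interval, not a test result.

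**Step 5: LOCF.** No arithmetic applies, because the protocol gives no rate of new bacteriuria. Section 3.3 supports the statement that a value carried forward while the catheter would still have been in place tends to be too low. It concerns bacteria in the catheter and says nothing of urine after removal, so it gives no direction for a value carried to the day 30-45 visit.

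**The case against.** A reader might infer that early device failures vanish from the safety results. The protocol does not support that. Section 13 never assigns the adverse event, discontinuation or tolerability analyses to the ITT cohort. Adverse events are recorded from consent, all variables are listed individually (section 13), and serious events are discussed case by case (section 13.4). Section 7.5 even requires end-of-treatment assessments of screened patients who never received the NO catheter. This stands: the denominator is unspecified, not shown to exclude these men, and what is at risk is the tabulated proportions and intervals.

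It can also be said that difficulty is not failure, that withdrawal under 7.5.2 is only permitted, and that a patient catheterised on day 1 may count as having had one day. The first two points make exclusion less frequent. The third would rescue some early removals but not a failed insertion. It may be added that analysis sets are often assigned to endpoints in the SAP. That would answer a bare omission, but here the protocol fixes three cohorts, and the entry rule common to all of them is the problem.

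On LOCF, a reader might infer that men withdrawn early are routinely turned into culture-negative ones, to the advantage of the arm with more failures. The protocol does not support that either. Section 8.6 asks for end-of-treatment assessments promptly after premature removal, and section 7.4 includes catheter and urine cultures among them. Sections 7.5 and 7.5.1 keep early discontinuers under follow-up. LOCF is discretionary, does not remove anyone from a cohort, and has no evident role in counts of adverse events or discontinuations. Bacteriuria is an observational endpoint. What survives is narrow: where a culture is missing despite these provisions, the carried value may mislead.

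**Conclusion.** The point holds in a limited form. All three cohorts named in section 13.3 inherit an entry rule that depends on device performance, and no cohort of all exposed patients is named. A patient with failed insertion is in none of them, and a patient with removal within a day may be in none of them. He can therefore be missing from the primary safety and tolerability proportions and their intervals, while still appearing in the listings.

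In a group of 6, one such patient who discontinues for an adverse event moves the estimate from 17% (0.4 to 64%) to 0% (0 to 52%). This assumes that one of the named cohorts is used as denominator, that he is not replaced, and that no other patient in the group discontinues for an adverse event. Because the study is descriptive and claims no power, these proportions and intervals are its main tabulated result on discontinuation.

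The LOCF point is secondary. It affects observational cultures only when they are missing, and its size cannot be derived from the protocol.

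**What to change.** 1. Add to section 13.3 a safety cohort of every patient in whom insertion of a study catheter was attempted, analysed by catheter type.
2. Name that cohort as the denominator for the section 5.1 endpoints and for the tolerability analysis in section 13.4.
3. Replace LOCF for cultures, laboratory values and vital signs with observed values, and report the number missing at each time point.

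The cost is a few lines of protocol or SAP wording and minor programming. Adverse events from consent onward, and catheter placement and removal dates (section 18.2), are already collected. The drawback for the sponsor is a possibly less favourable adverse event rate, since early failures would count. Some later time points would also rest on fewer values once nothing is carried forward.
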